### Eligibility Criteria

#### Inclusion Criteria

The inclusion criteria included:

Patients who signed ICF, including enrollment in the registry database (QiN-registry)Patients with stage 5 CKD treated with chronic hemodialysisPatients who are vaccinated against pneumococcal infection in accordance with current STIKO recommendationsPatients who were 18 years or older

#### Exclusion Criteria

The exclusion criteria included patients unwilling or ineligible for vaccination against pneumococcal infection under current STIKO recommendations.

A subject may withdraw from the clinical trial at any time for any reason without consequences. Discontinuation from the study will have no influence on the availability of vaccination for that patient. In case of premature discontinuation, the reason for discontinuation should be collected, but it is not obligatory. In the event of withdrawal, all blood samples will be destroyed according to data protection requirements. Data cannot be removed from already-completed studies or scientific analyses. A subject who discontinues the trial will not be replaced.

### Enrollment of Study Subjects

Eligible study subjects will be identified by their dialysis physician. If the subject does satisfy eligibility criteria and signs the ICF, he or she will be enrolled into the Duration of Protection From Pneumonia After Pneumococcal Vaccination in Hemodialysis Patients (DOPPIO) study by entering their data into the enrollment log and registering the subject in the eCRF. Basic data regarding vaccination history, underlying disorders, and so on will be captured directly in the study eCRF or transferred into the eCRF from the QiN database. The study’s conduct is illustrated in Figure 1.

Blood samples for pneumococcal antibody titer analysis will be drawn at baseline and every 3 months (with a range of 6 days). For newly vaccinated patients, baseline titers will be drawn 4 weeks after vaccination (Figure 1). A total of 6750 blood samples from 789 study subjects will be collected and analyzed.

**Figure 1 figure1:**
[figure not shown]
Schedule of vaccine titer assessments in the course of the Duration of Protection From Pneumonia After Pneumococcal Vaccination in Hemodialysis Patients (DOPPIO) study. *Decision for or against vaccination will be based upon the advice of the treating physician previously (along STIKO [Ständige Impfkommission]–criteria) and is not related to DOPPIO. eCRF: electronic case report form; QiN: quality in nephrology.

DZIF CTU study nurses will coordinate titer assessment schedules and inform participating physicians of upcoming blood samplings. Samples will be drawn over an existing venous or arteriovenous access before dialysis and thus constitute only a minimal additional burden for both patients and physicians. All titers will be analyzed at the end of the study. An enzyme immunoassay will be performed to detect the presence of pneumococcal antibodies.

### Management of Samples

For all subjects, 9 mL of blood will be collected in a 9-mL tube provided by the sponsor. Samples will be taken every 3 months after the baseline sample. For newly vaccinated patients, baseline samples will be taken 4 weeks after vaccination.

Immediately prior to the blood draw, the staff member performing the procedure will verify the subject’s identity. A label will be attached to the tube. The tube will be centrifuged within 3 hours after sampling. The tube will be shipped to the allocated DZIF site and frozen within 24 hours. Subject number, date of sampling, number of aliquots, date and time of preparation, and the subject’s consent are documented in a sample identification list at the KfH dialysis practices and recorded as source data. Samples will be stored at DZIF CTUs and sent frozen in 1 batch to the laboratory at the end of the study. Results will be transferred electronically to the study nurses at the end of the study for recording into the eCRF.

### Data Management Plan

The data will be recorded securely and electronically. The data are the sole property of the sponsor and must not be made available in any form to third parties, except for authorized sponsor’s representatives or appropriate regulatory authorities, without written permission from the sponsor. Data obtained from KfH via QiN becomes the property of the sponsor, as specified in the agreement between KfH and DZIF. Only data from enrolled patients will be transferred. The investigator will ensure that all data are entered legibly, completely, accurately, and conform to source documents.

The investigator will review and approve data, with the investigator’s validation serving as attestation of the investigator’s responsibility for ensuring that all data are complete, accurate, and authentic.

All information obtained during the study will be recorded digitally in conformity with the applicable laws and regulations.

### Ethics Approval

#### Overview

The study was approved by the lead Ethics Committee of the Medical Faculty of the University of Cologne (Cologne, Germany; No. 17-274) and subsequently received secondary approval by the 11 Ethics Committees of the respective DZIF CTU sites (ref. DZIF CTU site list, section study procedure).

The study was further approved by the Paul-Ehrlich-Institut (PEI), Federal Institute for Vaccines and Biomedicines, as a noninterventional study (NIS401) and registered at ClinicalTrials.gov with the identifier NCT03350425.

The study will be performed in accordance with all applicable laws and regulations, including the International Conference on Harmonization Guideline for Good Clinical Practice (GCP), the ethical principles that have their origins in the Declaration of Helsinki (current official version: World Medical Association [15]), and applicable privacy laws such as national laws and the General Data Protection Regulation, which has been in effect since May 25, 2018. The minimum required deidentified personal data will be captured in an electronic database, and any publication of study results will be anonymized, only containing summarized statistical analyses.

#### Subject-Informed Consent

KfH physicians will assist in setting up subject prescreening and informed consent procedures. Informed consent will be obtained by the treating physicians. The ICF will be signed prior to any study activities by the subject and treating physician conducting the informed consent process. No compensation is foreseen for study participants.

### Study Conduct and Statistical Analyses

The primary objective of this study is to compare pneumonia rates and outcomes between both groups. To achieve this, the raw number of events and raw rates of events per 100 patient years will be computed. For each group, the mean, median, SD, IQR, and minimum and maximum of demographical variables like age and sex will be computed. These observed variables will be used to build a Cox proportional hazard model. If applicable, this model will incorporate time-varying covariates and consider recurring events. To quantify the expected protective effect of a high titer level, multiple functional relationships will be explored, including but not limited to linear, quadratic, and step functions. Step functions will be created by dividing the titer levels into 10 mutually exclusive strata and estimating each risk individually. If possible, the largest difference between 2 neighboring strata will be identified as a threshold for an adequate titer level.

The secondary objectives of this study are to describe antibody titers as a function of time and factors influencing antibody kinetics. Descriptive statistics for titer levels at all intervals will be computed for absolute values as well as relative values (relative to the first observed or personal maximum). Levels for patients grouped by age, sex, and other variables of interest will be calculated. To allow a comparison, the mean, median, SD, IQR, and minimum and maximum titer levels will be calculated.

To identify which factors influence the absolute antibody titer level, multiple multivariate models will be built. In patients with available titers, risk factors for insufficient protection will be determined by multiple regression analyses of data including vaccination history and timing, medication exposure since last vaccination, history of underlying kidney disorder, dialysis, and demographic factors.

The titer levels will be assessed graphically by comparing boxplots of the titer levels at different time intervals. Concurrent titer levels will be tested for statistically significant differences by using a *t* test or a Mann-Whitney U test, whichever is applicable.

Differences in hospitalization as well as vaccination rates between KfH centers will be studied. QQ plots and tests for normal distribution will be performed on the observed hospitalization rates. Vaccination rates will be studied for outliers. For all factors used in model building, a region of common support will be established.

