**Methods:**

Within this prospective multicenter study, we aim to compare 2 strata of vaccinated patients: those recently vaccinated and those vaccinated more than 2 years ago. A total of 792 patients will be enrolled. Twelve partner sites (within the German Centre for Infection Research [DZIF]) with allocated dialysis practices participate in this study. All dialysis patients who are vaccinated against pneumococcal infection in accordance with Robert Koch Institute guidelines prior to enrollment will be eligible. Data on baseline demographics, vaccination history, and underlying disease will be assessed. Pneumococcal antibody titers will be determined at baseline and every 3 months for 2 years. DZIF clinical trial units coordinate titer assessment schedules and actively follow-up on study patients for 2-5 years after enrollment, including validation of end points of hospitalization, pneumonia, and death.

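### Relative titers are anchored to the first or highest observed sample and models target the titer level, so neither measures decline since vaccination or the factors that speed it

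*Protocol article*

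**What the plan says.** The Explorative Objectives name time since vaccination as the axis for describing titers and ask which factors influence antibody kinetics. The Conclusions repeat that axis. The Scientific Rationale is more specific and promises to find predictors of a faster decline.

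Study Conduct and Statistical Analyses restates the aim as to "describe antibody titers as a function of time and factors influencing antibody kinetics", without giving the origin of time. It continues: "Descriptive statistics for titer levels at all intervals will be computed for absolute values as well as relative values", where the relative values are defined as "relative values (relative to the first observed or personal maximum". To find factors that influence the absolute titer level, "multiple multivariate models will be built". Risk factors for insufficient protection come from multiple regression, with vaccination history and timing among the inputs.

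On sampling, the Abstract states: "Pneumococcal antibody titers will be determined at baseline and every 3 months for 2 years". Enrollment of Study Subjects adds: "For newly vaccinated patients, baseline titers will be drawn 4 weeks after vaccination". Management of Samples and Study Design say the same. No post-vaccination anchor is given for any other patient.

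**The concern.** A ratio measures decline since vaccination only if its denominator is taken at a known and common point after vaccination. Here that holds for newly vaccinated patients alone. Everyone else enters the study at whatever point of the curve enrollment finds them. The article's Background says that titers seem to fall substantially within 6 to 12 months, so on its own premise much of the fall in earlier-vaccinated patients precedes the value that is set to 100%. Those patients would look stable because their decline is already over.

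The personal maximum does not repair this. It too is confined to the observed period. It can also follow a revaccination, because vaccinations continue as routine care (Study Design).

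The second part concerns the models. Their named outcomes are the absolute level and insufficient protection. The question is about kinetics, that is, how fast titers fall and in whom. A factor that lowers the initial response and one that speeds waning can produce the same level. At stake is how the study describes the course of titers and which patients it reports as losing antibody faster.

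**Working it through.** The article states no sample size, power or error rate for the titer analysis, so there is no figure of its own to reproduce.

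**Inputs from the article**
- First sample at 4 weeks after vaccination for newly vaccinated patients only (Enrollment of Study Subjects).
- Follow-up samples every 3 months for 2 years (Abstract).
- At the interim, 596 patients vaccinated less than 2 years ago and 114 at 2 or more years (Amendment After Interim Study Report): 114/710 = 16%. At least these 114 lack the 4-week anchor. The 596 are not all newly vaccinated, and the article does not say how many are.
- 6750 samples from 789 subjects (Enrollment of Study Subjects): 6750/789 = 8.6 per subject.

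**Assumptions (not in the article)**
- Titer at t months after vaccination, relative to the initial level: g(t) = f + (1 − f)·exp(−k·t), with k = ln 2 / half-life.
- Half-life of the part above the floor: 6 or 12 months. Floor f: 0, 10% or 20%.

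**Step 1. Ratio to the first observed titer, 24 months later.** For a first sample at month s, the reported ratio is g(s + 24)/g(s). The decline since vaccination that the objective asks for is g(s + 24)/g(1).

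Example with half-life 12 months and floor 10%: g(1) = 0.950, g(25) = 0.312, g(30) = 0.259, g(54) = 0.140.
- First sample at month 1: 0.312/0.950 = 0.33.
- First sample at month 30: 0.140/0.259 = 0.54.
- True level of the second patient relative to month 1: 0.140/0.950 = 0.15.

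| Half-life (months) | Floor | Ratio, first sample at month 1 | Ratio, first sample at month 30 | True level at month 54 relative to month 1 |
|---|---|---|---|---|
| 6 | 10% | 0.17 | 0.79 | 0.11 |
| 6 | 20% | 0.27 | 0.90 | 0.22 |
| 12 | 10% | 0.33 | 0.54 | 0.15 |
| 12 | 20% | 0.41 | 0.69 | 0.25 |
| 6 | none | 0.06 | 0.06 | 0.002 |
| 12 | none | 0.25 | 0.25 | 0.05 |

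A first sample at month 12 lies between: with a floor, the ratio is 0.35 to 0.53, against a true level relative to month 1 of 0.13 to 0.31.

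With a floor, the ratio depends strongly on when the patient enrolled. Without one, it does not depend on enrollment time, but it still leaves out all decline before enrollment.

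**Step 2. Level versus rate.** Take no floor and look at month 12. A patient with the full initial response and a 6-month half-life is at 2^(−12/6) = 0.25. A patient with half the initial response and a 12-month half-life is at 0.5 × 2^(−12/12) = 0.25. The levels are equal, but only the first patient wanes faster. Vaccination timing as a regression input adjusts the level for elapsed time. It does not let the rate of fall differ by factor unless a factor-by-time term or a patient slope is added.

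**The case against.** The best defense is that the text is open rather than wrong. Absolute values are reported beside the relative ones. Vaccination timing and medication exposure since the last vaccination enter the regressions, so time since vaccination is not ignored. The relative values are descriptive, the objective is labeled explorative, and the primary comparison, the sample size and its error rate are untouched. All of this stands, and it limits the weight of the point. It does not give the ratio a common origin, and it does not turn a model of level into a model of decline.

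A reader might infer more from the section. The article does not support these stronger readings:

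- **That titers are analyzed by study visit.** The section speaks of intervals and does not define them. The objective names time since vaccination.
- **That the regressions ignore repeated samples.** The article neither states nor excludes a method for them, and such detail may sit in the full protocol or analysis plan, which are not shown.
- **That the t or Mann-Whitney tests ignore repeated samples.** The sentence is "Concurrent titer levels will be tested for statistically significant differences". Read as two groups compared at one interval, this uses one sample per patient. Simulated with 789 patients, such a t test at a nominal 5% rejected in 4.9% and 6.6% of 1000 runs at assumed within-patient correlations of 0.5 and 0.8 (simulation noise about 1.4 points).
- **That standard errors of decline are too small.** Even if samples were pooled as independent, the standard error of a within-patient time slope would be too large: simulated rejection was 0.3% and 0.0% at the same correlations. Only between-patient factors would have standard errors that are too small, and only under a pooling that the article does not describe.

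Survivor effects and pandemic gaps in sampling are possibilities, not errors in the text. The Limitations already mention interrupted serological observation.

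**Conclusion.** The point holds in two parts. First, relative to the first observed titer or the personal maximum, titers have no common origin in time since vaccination. For earlier-vaccinated patients the ratio omits decline before enrollment, and it cannot be compared across patients. This part follows from the sampling rule alone. Its size (0.54 to 0.90 reported where the true level relative to month 1 is 0.11 to 0.25) depends on the assumed half-life, floor and a first sample at month 30. Second, models of the absolute level do not by themselves answer the question about kinetics.

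The consequence is limited to an objective called explorative in the objectives and secondary in the analysis section. No claim is made about type I error or about standard errors that are too small. The change is worth making because, according to Results, statistical and laboratory analyses are still ongoing.

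**What to change.** In Study Conduct and Statistical Analyses:

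1. Name time since last vaccination as the time axis for all titer summaries and plots, and report geometric means along it. Restart the clock at a revaccination.
2. Limit values relative to the first observed titer to patients who have the 4-week post-vaccination sample. Do not use the personal maximum as a measure of decline.
3. For kinetics, fit a linear mixed model to log titer with time since last vaccination, patient random effects, the listed factors, and factor-by-time interactions. The interactions answer the question about faster decline. The random effects also account for the roughly 8.6 samples per patient, whatever the full plan says about them.

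The cost is revised wording, standard software and slightly more analysis work. Relative values would be reported for fewer patients. No new samples or data collection are needed, provided that vaccination dates are recorded as part of the vaccination history.

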Participating sites will screen all hemodialysis patients at their outpatient dialysis clinic for eligibility. Eligible patients will be approached and informed by their physicians. If a patient agrees to participate in the study and signs an informed consent form (ICF), basic data regarding vaccination history, underlying disease, and so on will be entered or imported electronically into the study eCRF. Pneumococcal antibody titers will be drawn at baseline and every 3 months. For newly vaccinated patients, baseline titers will be drawn 4 weeks after vaccination. Deutsches Zentrum für Infektionsforschung (DZIF; English: German Center for Infection Research) clinical trial units (CTUs) will coordinate titer assessment schedules and inform the participating physicians of upcoming blood samplings. The samples will be taken on dialysis days from an already inserted-intravascular catheter. DZIF CTUs will actively follow up on study patients for 2-5 years after enrollment. This follow-up will include validation of all hospitalizations and deaths documented in the electronic registry to assess whether the primary end point (all-cause pneumonia) occurred. During months 25-30, only the primary end point will be recorded (ie, no blood samples will be taken). Additionally, dialysis units will be contacted every 6 months to assess if pneumonia occurred that did not require hospitalization. Blood samples will be stored frozen at DZIF CTUs, and titers will be analyzed at the end of this study. All therapies and diagnostics, including vaccinations, will be administered solely as part of the clinical routine and as recommended by appropriate guidelines (eg, RKI Ständige Impfkommission [STIKO] recommendations). Thus, Arzneimittelgesetz (AMG) does not apply to this study, and participating physicians do not require Good Clinical Practice (GCP) certification.

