### Study Procedure

In principle, all KfH dialysis practices will be eligible to participate in this study. KfH practices can be considered representative of the German dialysis population since they are widely distributed throughout Germany and about 20%-25% of all hemodialysis patients are treated there. Site selection will depend on the willingness of the attending physicians to participate and key characteristics of the practice (eg, site location and number of patients). Criteria for site selection will be developed by QiN-group and DZIF-Köln. A number of suitable KfH dialysis practices will be allocated to each of the 12 DZIF CTU sites: Universitätsklinikum Bonn, Medizinische Klinik Borstel, Universitätsklinikum Eppendorf, Universitätsklinikum Gießen und Marburg, Standort Gießen, Medizinische Hochschule Hannover, Universitätsklinikum Heidelberg, Universitätsklinikum Köln (AöR), Universitätsklinikum Schleswig-Holstein/Campus Lübeck, Universitätsklinikum Gießen und Marburg, Standort Marburg, Klinikum der Universität München, Technische Universität München, and Universitätsklinikum Tübingen.

QiN-group will assist DZIF CTU personnel with site selection and internal KfH study participation formalities. DZIF CTU personnel will cooperate with the KfH physicians to assist in setting up subject prescreening and informed consent procedures. Informed consent will be obtained by treating physicians.

The sample size has been calculated to demonstrate a significantly lower all-cause community-acquired pneumonia (CAP) rate in newly vaccinated patients compared to patients vaccinated more than 2 years before enrollment.

The incidence of pneumonia in hemodialysis patients was reported as 29.0/100 patient-years (py) [14]. Data on the efficacy of pneumococcal vaccines for preventing pneumonia in hemodialysis patients is lacking. However, a recent meta-analysis demonstrated pneumococcal vaccination to result in a relative risk for pneumonia of 0.72 (95% CI 0.69-0.94) in an immunocompetent target population (ie, adults at risk or >65 years) [8].

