In general, immunological studies in hemodialysis patients have been carried out with limited patient numbers and in mixed populations (CKD, hemodialysis, and renal transplant recipients) [9]. Most studies suggest good initial immunogenicity, but titers seem to significantly decline after 6 to 12 months in adult dialysis patients [10]. The limited number of studies with longer follow-up periods suggests a possible benefit of revaccination after 2 years [11,12].

For the purpose of this calculation, we assume protection from pneumonia in the first 2 years to be equal to the protection recently demonstrated in an adult immunocompetent target population (relative risk 0.72) and afterward return to baseline. Thus, expected rates of pneumonia are 29.0/100 py in patients vaccinated >2 years ago and 20.88/100 py in patients vaccinated <2 years ago, respectively. To demonstrate the superiority of a more recent vaccination in preventing pneumonia with α=.05 and (1–β)=0.80, we would thus require 2 groups of 442 patients each (884 patients overall). Furthermore, the rate of pneumonia is also likely to be greater in an underprotected population than seen in the overall hemodialysis population, which includes a relevant number of freshly vaccinated patients. Additionally, the possibility of an unbalanced distribution of recently vaccinated patients (in a ratio of up to 1:7) was considered. A first statistical analysis will be discussed in an interim study report after 18 months.

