## Results

The study has enrolled 792 patients and the last follow-up has been completed. Currently, the statistical and laboratory analyses are ongoing.

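### Center differences in hospitalization are to be studied with normality tests, which address the shape of the distribution and not whether centers share one rate

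*Protocol article*

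**What the plan says.** The end of the Methods section Study Conduct and Statistical Analyses states an aim: "Differences in hospitalization as well as vaccination rates between KfH centers will be studied". The next sentence gives the procedure for hospitalization: "QQ plots and tests for normal distribution will be performed on the observed hospitalization rates". The one after it gives the procedure for vaccination: "Vaccination rates will be studied for outliers". The section names no comparison of hospitalization rates between centers, no model of hospitalization counts, and no purpose for the normality check.

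The article does not give the number of centers. Study Procedure says only: "A number of suitable KfH dialysis practices will be allocated to each of the 12 DZIF CTU sites".

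**The concern.** If the question is whether centers differ in hospitalization, the natural null is one common underlying rate. The null of a normality test is that the observed rates come from some normal distribution, of any variance. Centers that truly differ, with rates spread in a normal shape, satisfy that null. Centers with identical rates but few or unequal patient-years can break it, because small-center rates are skewed and rates from centers of different size have different precision. The named test can therefore miss real differences and can reject because of center size alone.

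What is at stake is the description of center variation. If it rests on the normality result, it says little about how much centers differ.

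**Working it through.** **1. Inputs.** The plan has no figure for this analysis, so there is none to reproduce.
- Patients: 792 (Results: "The study has enrolled 792 patients and the last follow-up has been completed").
- Follow-up: Study Design says "DZIF CTUs will actively follow up on study patients for 2-5 years after enrollment"; 2 years were used.
- Assumed, because not given: 12, 30 or 60 centers; equal sizes, or unequal sizes (lognormal weights, SD 0.8, at least 3 patients); a mean of 0.5 or 1.5 hospitalizations per patient-year; Shapiro-Wilk as the normality test, at 5%.

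**2. What each test looks at.** Let center *k* have *y* events in *T* patient-years, with *y* ~ Poisson(λ*T*) and rate *r* = *y*/*T*. Equality means that λ is the same in all centers. The normality null is *r* ~ N(μ, σ²) with μ and σ² free, and Shapiro-Wilk does not change when the rates are shifted or rescaled.

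Missed differences: 12 equal centers have 792/12 = 66 patients, 132 patient-years and, at 0.5 per year, 66 expected events each. With equal true rates, the squared coefficient of variation (CV) of the observed rates is 1/66 = 0.0152. With a true between-center CV of 20%, it is 0.0152 + 0.20² = 0.0552, or 3.6 times as large. That excess spread is the center difference, and Shapiro-Wilk disregards it.

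Equal centers flagged: 60 equal centers have 13.2 patients and 13.2 expected events each. The Poisson skewness is 1/√13.2 = 0.28, against 1/√66 = 0.12 with 12 centers. With unequal sizes, the variance λ/*T* also differs between centers, so the pooled rates have heavier tails than a normal distribution.

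**3. Simulation, Poisson counts, 2,000 runs per scenario.** Entries are the percentage of runs rejecting at 5%. True rates are equal, or normally spread with a CV of 20% or 30%. The comparator is a Poisson chi-square test of equal rates.

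| Centers | Sizes | Rate | Shapiro-Wilk: equal | CV 20% | CV 30% | Equal-rates test: equal | CV 20% | CV 30% |
|---|---|---|---|---|---|---|---|---|
| 12 | equal | 0.5 | 5.0 | 5.0 | 4.6 | 4.9 | 91.2 | 99.0 |
| 12 | equal | 1.5 | 4.8 | 4.8 | 5.5 | 4.2 | 99.9 | 100 |
| 12 | unequal | 0.5 | 14.6 | 6.2 | 5.3 | 6.2 | 88.1 | 98.0 |
| 12 | unequal | 1.5 | 12.7 | 5.1 | 4.7 | 4.1 | 99.2 | 100 |
| 30 | equal | 0.5 | 8.4 | 8.6 | 8.2 | 4.6 | 86.4 | 99.7 |
| 30 | equal | 1.5 | 6.0 | 5.8 | 4.9 | 5.0 | 100 | 100 |
| 30 | unequal | 0.5 | 25.9 | 15.3 | 12.1 | 6.1 | 84.1 | 99.2 |
| 30 | unequal | 1.5 | 24.8 | 8.5 | 7.3 | 4.9 | 99.9 | 100 |
| 60 | equal | 0.5 | 19.9 | 22.8 | 23.1 | 5.9 | 74.8 | 99.4 |
| 60 | equal | 1.5 | 9.9 | 9.8 | 6.9 | 5.3 | 100 | 100 |
| 60 | unequal | 0.5 | 36.9 | 32.0 | 32.5 | 5.6 | 75.1 | 98.7 |
| 60 | unequal | 1.5 | 31.7 | 16.5 | 12.6 | 5.7 | 99.9 | 100 |

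With equal sizes, Shapiro-Wilk hardly moves when real differences are added. With unequal sizes, it rejects less often when centers differ, because the normal spread of true rates outweighs the size-driven noise.

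**4. Allowing for repeat admissions.** Patients differ in their tendency to be admitted, so counts are likely to be overdispersed. Two further sets of runs used unequal centers, gamma patient frailty and, for differing centers, a true between-center SD of 25% of the mean. Figures are for 12, 30 and 60 centers.
- Frailty variance 0.5 or 1.0: Shapiro-Wilk rejected in 9–11%, 18–21% and 32–45% with equal rates, and in 6–8%, 14–23% and 40–62% with differing rates. An overdispersed Poisson test rejected in 4–6% with equal rates and had power 0.81–0.98, 0.72–0.98 and 0.57–0.96.
- Frailty variance 0.5 only: Shapiro-Wilk rejected in about 10–11%, 22–23% and 40% with equal rates, and in about 5–6%, 16–18% and 42–48% with differing rates. An overdispersed Poisson test rejected in about 5–10% with equal rates and 83–98% with differing rates.

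**The case against.** The text never says that the normality test decides whether centers differ. It states no null of equal rates and no consequence of a normal or non-normal result. Two ordinary readings are open. The check may be preliminary to choosing a method; the same section lets the choice between a t test and a rank test for titers depend on what applies. Or it may be a descriptive screen for unusual centers, parallel to the outlier inspection of vaccination rates, and a QQ plot is a fair tool for that. Center differences in hospitalization appear in neither the Primary Objective nor the Explorative Objectives. The article is condensed, and an unseen analysis plan may add a model. The simulation inputs are assumed, the QQ plot was not evaluated, and part of the false flagging comes from assumed size imbalance.

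Most of this stands, and it limits the point. It does not remove it. The article names a specific method directly after a specific aim, the method does not address that aim, and no later comparison is named that a normality check would serve. That is a poorly chosen method, not a missing detail. The lack of response to excess spread follows from the definition of the test; only the percentages depend on the assumed inputs.

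A reader might also infer that a normal result will be taken as proof that centers do not differ. The article contains no such rule.

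**Conclusion.** The point holds in a limited form and is minor. Normality tests on the observed rates do not answer whether KfH centers share one hospitalization rate. Under the assumed settings they reject in about 5–45% of runs when all centers are equal, depending on the number and size of centers. They respond little, not at all, or in the wrong direction when centers differ. Tests of equal rates stay at about 4–10% under equality and mostly exceed 70% power; the lowest figure is 0.57, with 60 centers and frailty.

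Three stronger readings are not supported:
- That the test never responds to center differences. With 60 centers and frailty, its rejection rate does rise modestly, and a single outlying center could show in a QQ plot.
- That rates ignore patient-years. A rate contains its denominator; what an unweighted display ignores is unequal precision.
- That a missed center difference would distort the primary pneumonia comparison. Hospitalizations are one route to pneumonia events, but Study Design adds six-monthly contact with the dialysis units for cases not admitted, and Data Collection explains that admissions are captured dependably because billing relies on them. The article shows no effect on the primary comparison.

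**What to change.** State that center differences in hospitalization will be studied with a negative binomial or overdispersed Poisson model of hospitalization counts, with log patient-years as offset and a center random effect. Report the between-center SD with its confidence interval, and show centers in a funnel plot of rate against patient-years. Keep QQ plots and normality checks only as descriptive displays or model diagnostics, for example on the estimated center effects, and say that this is their role.

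The cost is a few lines in the analysis plan, one model and one plot, on data already collected. The Results section says that the statistical analyses are still under way, so the change needs no new data and leaves the primary analysis untouched.
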